### Setting

The study will be conducted over the internet and by telephone so we will recruit from around the UK. The intervention will be delivered on the internet, with the guided version being supported by trained staff at the University of Exeter.

### Participant inclusion criteria

Participants will be young adults resident in the UK aged 18 to 24 years and with elevated RNT, defined as scoring above the 75th percentile on at least one measure of worry/rumination (≥50 on the PSWQ [40] and/or ≥ 40 on the RRS [15]). Additionally, participants must be able to understand written English to engage with the intervention and have private internet access to ensure confidentiality. In line with standard practice, participants currently receiving antidepressant medication will be eligible, provided the dosage has been stable for at least the previous month.

### Participant exclusion criteria

Because this is a prevention study, participants will be excluded if they meet diagnostic criteria for a current (within past month) major depressive episode. Additionally, potential participants will be excluded if they report current and significant substance abuse or dependence; current symptoms of psychosis or bipolar disorder; current psychological therapy; or active suicide risk.

### Recruitment procedure

The main recruitment pathway involves contacting university departments around the UK by email and asking them to circulate an advert to their undergraduate students (as successfully used by Kingston et al. [48]). Generic discipline email addresses, or named individuals within the departmental administration team where possible, will be obtained using internet searches. Departments will be asked to circulate an included advert in the form of an attached pdf, containing a hyperlink to an online trial website that provides information and the initial online screening measures, to undergraduates within their department. The pdf format ensures departments can display the advert as a poster if they are not permitted to circulate by email. The number of emails sent out each week will be modulated depending on the response rates.

A Facebook and Twitter account will be set up to help circulate the advert, particularly to non-students. Relevant organisations working with young people and/or mental health issues will also be asked to advertise a link to the study on their website.

### Screening, baseline and consent procedure

#### Initial Online screening

An online screening website will be used to identify potentially eligible participants. A brief introduction to the study is included on the introductory page. Consent to online screening is obtained by informing potential participants that by clicking continue on this introductory page they are consenting for their responses to be stored by the researchers and that this data is subject to the Data Protection Act 1998.

A series of short questionnaires is then presented to identify potentially eligible participants by collecting basic demographic information (age, sex, ethnicity, location, and how they learned of the study) and screening on shortened versions of the PSWQ (four items, range 4 to 20, cut-off ≥ 12) and RRS (five items, range 5 to 20, cut-off ≥ 10) as used by the Dutch trial to identify individuals with elevated RNT (that is, > 75^th^ percentile) and the PHQ-8 [49] (PHQ-9 minus the suicidal thought question) to exclude participants who are likely to meet a diagnosis for current depression (cut-off ≥ 15).

Automated feedback informs participants whether they are eligible for further screening. Those excluded on low worry/rumination are informed that worry and rumination do not appear to be a significant problem for them and are thanked for their interest. Those excluded on high PHQ score are given a message explaining that their scores indicate low mood which is affecting their quality of life and that they may be experiencing an episode of clinical depression. This message advises them to see their GP and provides contact details of organisations offering support and advice. Eligible participants are invited to leave their contact details (name, telephone number and email address) as consent to be contacted. The full information sheet and consent form are then sent by email to the participant with an invitation to participate in a telephone interview with the researcher. The full information sheet (Additional file 1) and consent form (Additional file 2) are then sent by email to the participant with an invitation to participate in a telephone interview with the researcher.

#### Telephone screening and baseline assessment

The researcher will provide the interviewee with an overview of the trial, conduct the clinical interview and ask for verbal consent. Interviews will be audio-recorded, with the participant’s consent, so that the diagnostic status can be independently rated. The screening interview consists of brief screening questions on alcohol and drug use; symptoms of bipolar disorder and psychosis (Psychosis Screening Questionnaire, PSQ [50]); assessment of any relevant past or current treatments; and the Structured Clinical Interview for DSM-IV (SCID-I; [43]) sections on current and past depressive episodes, dysthymia and any relevant anxiety disorders and eating disorders. As the primary objective of this study is to investigate the prevention of depression, anxiety and eating disorders will be measured, but participants meeting the criteria for a disorder will not be excluded from this study.

Excluded participants are given feedback including advice to visit their GP and contact details of organisations for further support. Additionally, any risk reported during the interview is assessed using a well-established protocol to ensure that appropriate clinical support is obtained. Eligible participants are then asked to complete baseline measures, assessing episodic stress (the Episodic Life Event Interview, part of the UCLA Life Stress Interview [51]); levels of worry and rumination (PSWQ and RRS); symptom severity of depression and generalized anxiety (PHQ-9 and GAD-7); neuroticism (Eysenck Personality Questionnaire-Revised Neuroticism sub-scale (EPQ-R; [52]) and history (family history of depression, experience of abuse in childhood). With the exception of the episodic stress interview, which is always completed during the interview, baseline measures can be completed during the telephone interview, or returned by email/post.

#### Consent to trial

All eligible participants will then be invited to enter the trial and asked to return the written consent to participate. Once consent is received, the participant will be randomised (see Fig. 1).

**Fig. 1 Fig1:**
[figure not shown]
CONSORT diagram

### Randomisation and allocation concealment

Independent computer-generated block randomisation to the guided i-RFCBT, unguided i-RFCBT or the no-intervention control group will be used. Randomisation will be stratified by sex and by past history of depression (presence or absence of past depressive episodes) to assess the effect of sex on outcomes and to examine potential differences between prevention of first onset and relapse prevention. The randomisation uses blocks of three to ensure close parity of randomisation across the intervention arms across time. Because of the two levels of stratification by sex and by level of depression, with blocks of three, the researcher would not be able to anticipate or determine allocation easily, and the use of varying block sizes was therefore deemed unnecessary. In order to preserve blinding of the study researcher, randomisation will be conducted by a third party not involved in assessing or treating the participants, and this third party will also inform the therapist, who will be responsible for informing participants of their allocation.

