### Sample for quasi-phase II pilot arm

In the absence of any data on the unguided i-RFCBT, no power and sample size calculation was conducted for this arm. We will therefore aim to recruit the same number of participants for this arm as the other arms (n = 78), giving a total sample size of 234. The inclusion of this intervention arm is to explore the feasibility of this unguided intervention with respect to attrition, acceptability and estimates of incident rate and effect size.

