### Blinding

This is a single blind study, with the researcher conducting outcome measures while blind to allocation. Participants will be asked at the end of the screening interview not to disclose their allocation to the researcher in any of their future correspondence with the researcher and reminded of the importance of this prior to and during each follow-up interview. Due to the intervention, participants and therapists cannot be blinded.

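### With fixed blocks of three, one participant's disclosed allocation narrows or reveals others' in the same block, and stratification does not prevent this

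*Protocol article*

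**What the plan says.** Under *Randomisation and allocation concealment*, the protocol article states: "Independent computer-generated block randomisation to the guided i-RFCBT, unguided i-RFCBT or the no-intervention control group will be used". There are four strata (sex by past history of depression). On block size: "The randomisation uses blocks of three to ensure close parity of randomisation across the intervention arms across time". It then reasons that, because of the stratification, "the researcher would not be able to anticipate or determine allocation easily, and the use of varying block sizes was therefore deemed unnecessary". A third party who neither assesses nor treats participants randomises and tells the therapist, who tells the participant.

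Sex is collected in the online screen (*Initial Online screening*). The researcher conducts the diagnostic interview covering past depressive episodes (*Telephone screening and baseline assessment*). Randomisation follows receipt of written consent (*Consent to trial*). The SCID-I assessments fall at 3, 6 and 15 months from randomisation (*Follow-up assessments and outcome measures*).

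Under *Blinding*, the researcher measuring outcomes is blind and participants are not. Participants are asked "not to disclose their allocation to the researcher in any of their future correspondence with the researcher", and are reminded before and during every follow-up interview.

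**The concern.** Three is the smallest permuted block possible for three equally allocated arms, so every block is a single permutation of the arms. Stratification hides a sequence only from someone who cannot tell which stratum a participant is in. Here the researcher can, because both factors are established before randomisation, one of them in that researcher's own interview. The protocol does not say that the researcher knows order of entry, but consent and the follow-up schedule make it a reasonable inference.

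What is at stake is assessor blinding, the only blinding in the trial. The primary outcome, onset and timing of a major depressive episode, rests on interview judgement. With fixed threes, one participant's slip tells the assessor something about two others as well. The main route of harm is leakage to participants already randomised and still to be assessed.

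**Working it through.** The plan gives no predictability figure to reproduce.

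**Inputs**
- Arms: 3. Block size: 3, fixed. Strata: 2 × 2 = 4 (*Randomisation and allocation concealment*).
- Equal allocation, 78 per arm (*Sample for quasi-phase II pilot arm*, "giving a total sample size of 234"): 3 × 78 = 234 = 78 complete blocks.
- Probability *u* that a participant discloses: not given. Assumed 10%, 20% and 30%, independent between participants.
- Accrual time and stratum shares: not given. Assumed 12 to 30 months, with strata holding 5% or 25% of entrants.

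**1. No disclosure.** All six permutations of a block are equally likely. Knowing stratum and order leaves each arm at 1/3.

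**2. With disclosure.** One disclosed allocation moves each of the other two block members to 1/2; two disclosed allocations fix the third. If every earlier allocation were known, correct guesses would average (1/3 + 1/2 + 1)/3 = 61.1%, with one allocation in three certain.

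**3. A masked participant whose two block-mates have both had the chance to disclose.** Certain = *u*²; exactly one arm excluded = 2*u*(1 − *u*).

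| *u* | Certain | One arm excluded |
|---|---|---|
| 10% | 1% | 18% |
| 20% | 4% | 32% |
| 30% | 9% | 42% |

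**4. At the first follow-up.** If members are interviewed in entry order and disclose only then, the first has no earlier discloser, the second one possible, the third two. The averages are *u*²/3 certain and [0 + *u* + 2*u*(1 − *u*)]/3 excluded. At *u* = 20%: 0.04/3 = 1.3% and (0 + 0.20 + 0.32)/3 = 17%. The table therefore applies to later visits.

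**5. Bearing on the primary contrast.** The block-mates of a masked guided participant are one unguided and one control participant. Exactly one disclosure is equally likely to come from either. If it comes from the unguided member, guided and control stay equally likely. Half of the exclusions therefore carry no information on guided versus control. The informative share is *u*² + *u*(1 − *u*) = *u*; at 20%, 4% + 16% = 20%. The same holds for a masked control participant.

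**6. Upcoming allocations.** Time to fill a block = 3 / (234 / months × stratum share). With a 25% share: 3/(234/12 × 0.25) = 0.6 months, up to 3/(234/30 × 0.25) = 1.5 months. With a 5% share: 3.1 to 7.7 months. The first planned follow-up is at 3 months, so in larger strata a block is normally complete before a follow-up disclosure can occur. Only small strata leave a next allocation to predict.

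**7. Alternatives, if all earlier allocations were known** (exact for fixed sizes; for the mixed sizes, simulation with an optimal guesser who knows the set of sizes but not the current one).

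| Scheme | Certain | Guessed correctly |
|---|---|---|
| Fixed 3 | 33.3% | 61.1% |
| Fixed 6 | 20.0% | 56.1% |
| Mixed 3, 6 | about 8% | about 58% |
| Mixed 3, 6, 9 | about 4% | about 55% |

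**The case against.** The strongest reply is that allocations are properly withheld. A third party randomises, the assessor is never told, and the protocol claims only that allocation cannot easily be anticipated. Without disclosures nothing leaks, and the protocol asks for non-disclosure and repeats the request at every follow-up. Audio-recording for independent rating is also provided, although it is described for the screening interview and its use at follow-up is not stated. All this limits how often a leak starts. It does not stop a leak from spreading within a block, and the reminders show that the protocol regards disclosure as a live risk.

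The disclosure rates are assumptions, and the tabulated figures are upper ones, as steps 4 and 5 show. That stands in full.

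A reader might infer that the researcher can read off every third allocation from stratum and order. The documents do not support that: certainty requires knowing the other two allocations in the block. Nor do they show that disclosures will occur, that a single individual does all the assessments (the researcher is named as a role, without a headcount), or that upcoming allocations are generally predictable during recruitment.

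Finally, varying the sizes sharply reduces certainty (33% to about 4%) but reduces correct guessing only modestly (61% to about 55%), and it cannot help participants already randomised. That also stands.

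**Conclusion.** The reason given for not varying block size is wrong: stratifying on two factors known to the assessor does not protect a sequence of fixed threes. The weakness is real but conditional on disclosures by participants. At assumed independent rates of 10% to 30%, once both block-mates have had the chance to disclose, 1% to 9% of masked participants are revealed and a further 18% to 42% have one arm excluded. The figures are lower at the first follow-up, and about half of the exclusions do not bear on guided versus control. The result also rests on the assessor knowing order of entry, which is inferred. Prediction of upcoming allocations is secondary and mostly confined to small strata. This does not show that concealment failed or that the primary result is biased. It is an avoidable weakness in the trial's only blinding, and cheap to reduce.

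**What to change.** Recruitment was still open (*Trial status*). For the remaining participants, the third party should generate randomly varying permuted blocks, for example of 3, 6 and 9, within the same four strata, and withhold the sizes from the research team. Delete the sentence saying that varying sizes are unnecessary; this is warranted even if recruitment is nearly complete.

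The cost is a regenerated list and some loss of balance. The worst-case difference between two arms rises from 1 to 3 per stratum, or from 4 × 1 = 4 to 4 × 3 = 12 over the four strata. The latter needs every stratum to stop at its worst point in the same direction, which is unlikely in practice. Those already randomised gain nothing.

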### Sample size calculation for phase III efficacy trial

Power and sample size calculations were based on testing the primary question of the efficacy of guided internet-RFCBT in terms of reducing the onset of major depression relative to the no-intervention control. For our primary comparison of guided i-RFCBT versus the no-intervention control, the Topper et al. study using the binary outcome of number of individuals meeting caseness for depression at 12 months, reported 13.1 % incidence of depression in guided i-RFCBT and 32.2 % incidence in the no-intervention control (hazard ratio = 0.41). Assuming similar effect sizes to the Topper et al. study for our intended time-to-outcome survival analysis over 12 months, then to detect the hazard ratio of 0.41 between these arms at the two-tailed 5 % alpha level, 75 participants must be recruited to each arm to provide 86 % power.

Estimates for change in depressive symptoms pre-to-post intervention for the guided i-RFCBT relative to the waiting list control indicate that 78 participants per arm provide a power of 80 % to detect the observed effect size of d = 0.51 from the Dutch trial at the two-tailed 5 % alpha level, allowing for the 20 % follow-up drop-out attrition observed in the Dutch study.

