In a prevention trial of RFCBT, 251 students aged 15-22 with elevated worry and/or rumination (scoring on top quartiles of respective measures: ≥ 50 on Penn State Worry Questionnaire (PSWQ; [40]; ≥ 40 on Ruminative Response Scale of the Response Styles Questionnaire (RRS; [15])) but who did not currently meet diagnostic criteria for depression or generalized anxiety disorder were recruited, and randomised into face-to-face group RFCBT, internet-delivered RFCBT (i-RFCBT), or a no-intervention control group. Participants were assessed for symptoms and ‘caseness’ of depression and anxiety on standardised self-report measures (Patient Health Questionnaire, PHQ-9; [41]; Generalized Anxiety Disorder Screener, GAD-7; [42]) at baseline, post-intervention, 3 month and 12 month follow-ups. This study indicated the feasibility of recruiting and retaining participants for such a prevention study and indicated the acceptability of these interventions. Further, group RFCBT and internet RFCBT reduced worry, rumination, depression and anxiety symptoms significantly more than waiting list control. At 12 month follow-up, cumulative incidence rates for depression (estimated from “caseness” on PHQ-9) are reduced in the two RFCBT intervention groups (13.1 %) relative to controls (32.2 %). Moreover, reductions in rumination and worry were found to mediate the effects of RFCBT on symptom severity.

These findings are encouraging. However, there are several key limitations of the Dutch study: (a) there is not a diagnostic interview to determine incidence of major depression, with the study instead using self-report and only able to assess point prevalence rather than retrospective incidence; (b) similarly, it is not known whether the participants had previous episodes of depression, i.e., whether the intervention prevents first onset or relapse/recurrence of depression.

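### The stated 86% power for the primary endpoint does not follow from its inputs: 0.41 is a risk ratio, the implied hazard ratio is 0.36, and no drop-out is allowed for

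*Protocol article*

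**What the plan says.** All of the primary power statement is in the protocol article, section Sample size calculation for phase III efficacy trial.

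- The earlier Dutch trial, using a binary 12-month outcome, "reported 13.1 % incidence of depression in guided i-RFCBT" and "32.2 % incidence in the no-intervention control (hazard ratio = 0.41").
- Assuming a similar effect for a survival analysis over 12 months, "to detect the hazard ratio of 0.41 between these arms" at two-sided 5%, "75 participants must be recruited to each arm to provide" 86% power.
- The next paragraph covers symptom change (d = 0.51, 80% power). It reaches 78 per arm after allowing for the 20% "follow-up drop-out attrition observed in the Dutch study". No allowance is stated for the primary outcome.

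Three other sections bear on this. The section on the pilot arm sets 78 for every arm, 234 in total. The statistical analysis section makes Cox regression the primary analysis and censors participants who drop out of measurement. The Background says of the same Dutch trial that cumulative incidence rates for depression "are reduced in the two RFCBT intervention groups (13.1 %) relative to controls (32.2" %), that is, group-delivered and internet-delivered RFCBT.

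**The concern.** The effect is called a hazard ratio, yet it equals the ratio of two proportions from a binary outcome. Those are different quantities when a third of the control arm has the event. The stated power also looks high for so few expected events, and the drop-out that the plan itself expects appears in only one of the two calculations.

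This is the only power statement for the primary endpoint, and the abstract describes the trial as designed and powered for this comparison. If the figure is too high, a null result would be read against a sensitivity that the trial did not have.

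**Working it through.** **Inputs** (sample size section unless noted): control incidence 0.322; intervention incidence 0.131; stated hazard ratio (HR) 0.41; two-sided 5%; 75 per arm; 12 months; stated power 86%. Target of 78 per arm from the pilot-arm section. Drop-out of 20% from the symptom calculation.

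**1. What 0.41 is.** 0.131/0.322 = 0.407, the risk ratio. Under proportional hazards the same incidences give HR = ln(1 − 0.131)/ln(1 − 0.322) = (−0.1404)/(−0.3886) = 0.361.

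**2. Trying to reproduce 86% as stated.** With HR 0.41, intervention incidence is 1 − 0.678^0.41 = 0.147. Events = 75 × (0.322 + 0.147) = 35.2.

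- Schoenfeld: Φ(√35.2/2 × |ln 0.41| − 1.96) = Φ(2.645 − 1.96) = 75%.
- Freedman: Φ(√35.2 × (1 − 0.41)/(1 + 0.41) − 1.96) = Φ(2.482 − 1.96) = 70%.
- Simulated log-rank test, exponential times, 20,000 runs: 73%.

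Counting events from the stated 13.1% instead (34.0 events) gives 74% and 68%. For 86% power, (1.96 + 1.080)² = 9.24, so the events needed are 4 × 9.24/(ln 0.41)² = 46.5 (Schoenfeld) or 9.24 × (1.41/0.59)² = 52.8 (Freedman). The stated figure is not reproduced.

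**3. Using the HR that the rates imply.** Events = 75 × (0.322 + 0.131) = 34.0, or 35.3 at 78 per arm.

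| HR 0.361, no drop-out | Schoenfeld | Freedman | Simulation |
|---|---|---|---|
| 75 per arm | 84% | 78% | 81% |
| 78 per arm | 86% (85.7%) | 80% | 83.5% |

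A plain two-proportion test on 13.1% against 32.2% with 75 per arm gives 80%.

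**4. Adding 20% drop-out.** Two loss models bracket the answer: the 20% contribute nothing (60 of 75, or 62.4 of 78, remain), or they are censored at a constant rate that reaches 20% by 12 months.

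| | 20% contribute nothing (Freedman–Schoenfeld) | Constant-rate censoring (Freedman–Schoenfeld; simulation) |
|---|---|---|
| 75 per arm, HR 0.361 | 69–76% | 74–80%; 77% |
| 75 per arm, HR 0.41 | 59–66% | 65–71%; 68% |
| 78 per arm, HR 0.361 | 70–77% | 75–82%; 79% |
| 78 per arm, HR 0.41 | 60–67% | 67–73%; 70% |

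The low ends of the HR 0.41 rows (59% and 60%) count events from the stated 13.1%. With the 14.7% that HR 0.41 implies, they are 60% and 62%.

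**5. Cross-check.** The symptom calculation does reproduce: d = 0.51 at 80% power needs 61 per arm, and 61/0.8 rounds up to 77, against 78 stated. So the section handles attrition properly there, and the 78 adds only three per arm to the primary comparison.

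**6. Source of the 13.1%.** The sample size section presents it as the "incidence of depression in guided i-RFCBT". The Background says that rates "are reduced in the two RFCBT intervention groups", with the single figure of 13.1%. The documents give no internet-only rate, so no effect on power can be computed.

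**The case against.** **The mislabel works against the trial, not for it.** A reader might infer that calling a risk ratio a hazard ratio is what inflates the power, so that true power is 70–75%. The documents do not support that. Those figures hold only if 0.41 is kept as a genuine hazard ratio. The incidences are stated inputs too, and they imply the stronger effect of 0.36. On that reading, Schoenfeld gives 84% at 75 per arm and 85.7% at 78, so before drop-out the gap is small by that formula. This stands. It still requires a different hazard ratio and a different sample size from those in the sentence, and it does not survive drop-out.

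**The attrition model is an assumption.** The 20% is tied to the symptom outcome. The diagnostic interview recovers episodes between visits, so a missed interim visit need not lose an event, and multiple imputation is planned. This is a fair reason to give a range and not one post-attrition figure. It does not remove the point, because participants lost to measurement are to be censored.

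**Follow-up runs to 15 months.** Carrying the same hazards to 15 months gives, at 75 per arm without loss, 78–83% at HR 0.41 and 85–90% at HR 0.36. But the sample size section fixes 12 months, and the primary outcome is also defined over 12 months.

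**The pooled 13.1% may matter little.** The abstract says that the internet and group formats reduced onset equally. A reader might count the pooling as a further cause of lost power; nothing in the documents shows that it is. It is an inconsistency of attribution only.

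**Conclusion.** The power statement is wrong as written. HR 0.41 with 75 per arm over 12 months gives about 70–75% power, not 86%. The rates behind it imply HR 0.36 and about 78–84% at 75 per arm (80–86% at 78) before drop-out. With 20% loss at 75 per arm, the range is about 69–80% at HR 0.36 and 59–71% at HR 0.41. None of the 12-month calculations reaches 86% once drop-out is allowed for.

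These figures assume proportional hazards, the stated control incidence of 32.2%, two-sided 5%, and the two loss models above; the formula-based ranges run from Freedman to Schoenfeld. How the 86% was obtained cannot be established. Two calculations come near it: HR 0.361 with 78 per arm (85.7%), and HR 0.41 with the control rate applied to both arms (48 events, 87%). Neither is what the text describes.

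**What to change.** Rewrite the primary power paragraph, with no change to sample size, design or analysis:

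1. Delete the 86% claim.
2. Call 0.41 the risk ratio and give the implied hazard ratio, 0.36.
3. State the expected events at 78 per arm over 12 months: 35 without drop-out at HR 0.36, and about 28–32 with 20% drop-out.
4. State power at 78 per arm with 20% attrition, naming the formula and loss model: about 70–82% at HR 0.36 (79% by simulation with constant-rate censoring), and about 60–73% if the true HR is 0.41 (70% by simulation).
5. Reconcile the 13.1% with the Background: give the internet-only rate if it is available, or say that the figure pools both interventions.

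The cost is one paragraph and a less favourable stated power.
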